#### Arm 2: Resident Endorsement

The resident endorsement model (Arm 2) seeks to engage residents by using an empowerment/network-based approach to shift the culture of health in buildings that encourages residents to collectively tackle indoor smoking and secondhand smoke exposure via physical demarcations and/or social media. Buildings assigned to this arm will be targeted for a series of 2 in-residence programs that involve community forums and the creative arts to garner resident endorsements of smoke-free living environments. Premised on resident engagement, this arm seeks to impact social and physical dimensions of the residential environment to achieve compliance. The sessions will: 1) inform residents of risks associated with smoking and secondhand smoke; 2) identify reasons to have a smoke-free home, 3) ask residents to sign a pledge on paper and/or virtually; 4) display smoke-free signage on doors and/or social media pages with an original hashtag (#Smokefree[building address]); and 5) refer residents to the Smoke-free NYCHA website for information on the policy and existing cessation resources.

#### Arm 3: Combined Intervention

There will be buildings assigned to receive both models (Arm 3) for which in-residence programs based on the resident endorsement treatment and the smoking reduction/cessation treatment will be provided. Both will occur simultaneously with one geared toward all building residents (resident endorsement) and the other targeting smokers (smoking reduction/cessation) with the goal of reducing both personal smoking and secondhand smoke exposure.

The interventions and comparison group are outlined in Table 1.

### Criteria For Discontinuing Or Modifying Allocated Interventions {11b}

The criteria for discontinuing or modifying allocated interventions in any given building will be in response to any requests by overseeing building authority/management who may voice concerns about administering interventions and decline further participation of their building, and subsequently residents, in the study.

The criteria for discontinuing targeted intervention approaches like the reduction/cessation and combined interventions will be in response to participant request to discontinue or nonresponse.

### Strategies To Improve Adherence To Interventions {11c}

Interventions are administered by peer educators who will collect evaluations to assess quality of interactions and sessions. These are reviewed by researchers periodically to ensure participants are engaging with the activities in a meaningful way and appropriate protocols in delivering the interventions are followed. Research team members will also periodically attend sessions related to resident endorsement activities and meetings with participants related to the reduction/cessation activities to further ensure appropriate protocols are taken.

### Relevant Concomitant Care Permitted Or Prohibited During The Trial {11d}

Participants will not be restricted from pursuing additional/further tobacco reduction/cessation support services. We will make every effort to document any services provided by NYCHA during regular briefings, and also in assessments.

### Provisions For Post-trial Care {30}

For the reduction/cessation intervention, individuals interested in quitting will be provided a month supply of nicotine patches. There are limited risks and steps are taken to ensure those more likely to experience possible side effects are not provided patches. Peer educators will report any instance of harm to the Columbia research team who will then take action to remedy the situation as deemed appropriate and report the adverse event accordingly.

### Outcomes {12}

#### Primary Outcomes:

There are three primary outcomes being measured:

We will evaluate the change in number of cigarettes smoked per day using self-reported average number of cigarettes smoked per day among smokers measured at the time of baseline assessment, interim assessment (approximately 3 months post-intervention), and long-term assessment (approximately 12 months post intervention).We will evaluate change in salivary cotinine levels for 25% of the sample via passive drool collection among smokers and non-smokers collected at baseline assessment and the long-term assessment.We will evaluate change in secondhand smoke exposure via self-reported amount of exposure to secondhand smoke. This will be measured in all three assessments.

#### Secondary outcomes

There are 6 secondary outcomes being measured:

We will evaluate change in number of participants with successful quit attempts measured at baseline assessment, interim assessment, and long-term assessment for smokers.We will evaluate change in number of quit attempts using the mean number of quitting attempts among smokers measured at baseline, interim, and long-term assessments.We will evaluate change in number of participants with second-hand smoke observations who have either observed second-hand smoking or not measured at baseline, interim, and long-term assessments.We will evaluate change in number of hours of second-hand smoke exposure via self-reported number of hours of observing someone smoke indoors measured at baseline, interim, and long-term assessments.We will evaluate change in number of smokers via counted number of people observed smoking in common areas at building visits.We will evaluate change in number of cigarette butts via counted number of cigarette butts observed in common areas at building visits.

These outcome measures are summarized in Figure 5.

### Participant Timeline {13}

Consented, eligible participants will be in the study for up to 15 months once recruited. A staggered recruitment, data collection, and intervention delivery model will be implemented to ensure appropriate timing of participant involvement from recruitment to the final follow-up and to better align study resources across all 64 enrolled buildings (See Table 2.)

#### Sample Size {14}

Power analysis was conducted using software PASS.15 for the primary outcome (change in salivary cotinine over a year) in Aims 1 and 2. Sampling 16 clusters (buildings) with 4 subjects per cluster (smokers for Aim 1, non-smokers for Aim 2) in each arm, we have 128 subjects per group or 256 in groups with or without a specific type of treatment (e.g. resident endorsement vs. no endorsement, cessation vs. no cessation). We calculated effect size as group mean difference in unit of standard deviation (SD) of the outcome, based on a two-sided test for mean difference between two groups in a cluster-randomized design with power of 80%. To compare groups with and without specific type of treatment, the group size of 256 may detect effect size of 0.283SD, 0.299SD, 0.312SD at significance level alpha = 0.05 for intra-cluster correlation coefficient r = 0.1, 0.15, 0.2, respectively. To compare intervention arms to the control arm, we have 3 comparisons and use conservative Bonferroni adjustment for multiple tests on significance level that alpha = 0.0167 (= 0.05/3). The sample size of 128 subject per arm may detect effect size of 0.472SD, 0.499SD and 0.524SD for r = 0.1, 0.15 and 0.2, respectively, at alpha = 0.0167. To put these numbers in perspective, using mean and SD estimated from a study of smokers in Maryland, an effect size of 0.283SD would correspond to a mean difference in salivary cotinine between the two intervention groups of 55.3 ng/mL with group SD = 195.4 ng/mL for smokers and of 0.19 ng/mL with group SD = 0.672 ng/mL for non-smokers.124 For instance a mean difference in 5 cigarettes smoked per day in the same study was 59.6 ng/mL for smokers.124 In England, following the smoke-free legislation salivary cotinine declined from mean level of 0.36 to 0.07 ng/mL (mean difference 0.29 ng/mL) among non-smokers.125 These findings support that we have sufficient power to estimate the impact of our interventions. The study is powered on an 80% retention rate, which we have achieved in other studies. Reasons for attrition will be tracked; those lost to follow up will be compared to the final sample.

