## Data collection and management

### Plans For Assessment And Collection Of Outcomes {18a}

There are three assessments during this trial. These include a baseline assessment conducted upon recruitment and after building randomization, an interim assessment conducted over the phone approximately 3 months after the delivery of intervention, and a final long-term assessment conducted approximately 12 months after the delivery of intervention. The survey questionnaire collects information on housing conditions, indoor air quality, personal smoking behavior and cessation attempts, exposure to secondhand smoke, opinions on secondhand tobacco exposure, the smoke-free policy and tobacco policies, and health conditions. Additionally, passive drool samples from 25% of participants (n = 128) is collected at the time of the baseline assessment and at the final follow-up. Sensory building observations occur at the start of recruitment and during the final assessments to record signs of active smoking and/or tobacco/marijuana odor. The presence of cigarettes, cigars, ashtrays with/out ashes, matches or lighters will be documented within apartments and around the building premises including stairwells, elevators, hallways, laundry rooms, in/outdoor community spaces, playgrounds, and the perimeter of the buildings.

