### Primary outcome

1)

Self-reported average number of cigarettes smoked per day and secondhand smoking exposure (hours of secondhand smoke exposure in the building in the past 7 days) will be measured at baseline (in person interview), 3 months (phone interview) and 12 months (in person interview). Salivary cotinine will be measured for 25% of the sample at baseline and at the 12-month follow-up for smokers to evaluate reliability of self-reported smoking behavior in Aim 1 and for non-smokers to evaluate self-reported secondhand smoke exposure in Aim 2.

To examine the intervention group differences in the change of self-reported smoking (Aim 1), we will use GLMRM with identity link, E(Yijkh) = ßh + ßkhtk + ßZij, where Yijkh is an outcome variable (transformed if necessary) for smoking exposure measured at time tk (t0 = 0 for baseline; t1 = 1 for 6 months, 0 else; and t2 = 1 for 1 year, 0 else) from the ith participant of the jth building in the hth arm/group (h = 1, 2, 3, 4). For the reference group of h = 4, ßk4 = 0 for k = 0, 1, 2; so that parameter ßkh (k = 1, 2; h = 1, 2, 3 for intervention arm) indicates the difference in outcome change since baseline between intervention group h and reference group, and ß is a vector of coefficients for the vector of control variables Zij (if any). To examine if effect of treatment A depends on treatment B or vice-versa, we will test null hypothesis ßk1 = ßk2 + ßk3 for all k, which suggests independent effects of treatment A and treatment B and simpler model that E(Yijk) = ß0 + ß1A + ß2B + ßk0tk + ßk1tk A + ßk2tk B + ßZij with dummy variables A and B indicating treatment type. To examine the intervention group differences in the change in hours of secondhand smoke exposure in the building in the past 7 days for non-smokers, we will use GLMRM with log link (Aim 2). Models will be run with and without control variables (if any).

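### Stated power rests on cotinine in 128 per arm and 256 per factorial side; the plan yields about 16 and 32 saliva donors per aim, because counts are doubled and only 25% give saliva

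*Protocol article*

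**What the plan says.** In the protocol article, Sample Size {14} names one outcome for all its power figures: "Power analysis was conducted using software PASS.15 for the primary outcome (change in salivary cotinine over a year) in Aims 1 and 2". The design input is "Sampling 16 clusters (buildings) with 4 subjects per cluster (smokers for Aim 1, non-smokers for Aim 2) in each arm", followed by "we have 128 subjects per group or 256 in groups with or without a specific type of treatment". At 80% power, two-sided, it reports detectable effects for intra-cluster correlations (ICC) of 0.1, 0.15 and 0.2:

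- with versus without a treatment, 256 per side, alpha 0.05: 0.283, 0.299 and 0.312 SD;
- arm versus control, 128 per arm, alpha 0.0167: 0.472, 0.499 and 0.524 SD.

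It translates 0.283 SD into 55.3 ng/mL for smokers (SD 195.4) and 0.19 ng/mL for non-smokers (SD 0.672). It compares these with 59.6 and 0.29 ng/mL from two cited studies and concludes: "These findings support that we have sufficient power to estimate the impact of our interventions".

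Elsewhere the saliva sample is much smaller. The primary outcomes under Outcomes {12} include: "We will evaluate change in salivary cotinine levels for 25% of the sample via passive drool collection among smokers and non-smokers". Plans For Assessment And Collection Of Outcomes {18a} has "passive drool samples from 25% of participants" and gives the number as 128. The biological specimens section {33} applies the 25% within each building.

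Under Statistical methods, Primary outcome, saliva is collected "at the 12-month follow-up for smokers to evaluate reliability of self-reported smoking behavior in Aim 1", with a parallel validation purpose for non-smokers in Aim 2. The models written out there are for self-reported smoking and for hours of secondhand smoke exposure.

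**The concern.** The outcome that carries the whole power statement is measured in a quarter of the participants, and the sample-size section makes no allowance for this. The group sizes it uses are also too large for either aim, even if everyone gave saliva. Cotinine therefore has far less power than claimed. The self-reported outcomes, which are measured in everyone, have no power figure based on their own correct counts.

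Cotinine also holds three roles: the outcome the trial is powered on, one of three primary outcomes, and a reliability check. At stake is how a cotinine result can be read. With the planned saliva sample, a null result would say little about effects of the size the protocol itself uses as benchmarks.

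**Working it through.** **Inputs.** From Trial design {8}: 64 buildings, 16 per arm, and 4 smokers plus 4 non-smokers per building (512 participants). From Sample Size {14}: ICC 0.1 to 0.2, 80% power, two-sided alpha 0.05 (factorial) or 0.0167 (arm versus control), SDs 195.4 and 0.672 ng/mL, 80% retention. From {18a} and {33}: 25% give saliva, 128 in total, sampled within each building.

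**Formula.** With n per group in clusters of size m, the design effect is DE = 1 + (m − 1) × ICC, and the detectable effect in SD units is approximately d = (z for alpha/2 + z for power) × √(2 × DE / n). The non-central t version is used where groups are small.

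**Step 1: reproduce the stated figures.** With m = 4, DE = 1.30, 1.45 and 1.60.

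- Factorial, n = 256, ICC 0.1: (1.960 + 0.842) × √(2 × 1.30 / 256) = 2.802 × 0.1008 = 0.282. Across the three ICCs the t version (df 510) gives 0.283, 0.299 and 0.314, against 0.283, 0.299 and 0.312 stated.
- Arm versus control, n = 128, alpha 0.05/3, t with df 62: 0.472, 0.499 and 0.524, an exact match.

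So the stated figures need 256 / 4 = 64 clusters of 4 per factorial side and 128 / 4 = 32 clusters of 4 per arm. The trial has 32 and 16 buildings. Using 3.2 per cluster (80% of 4) does not reproduce the figures, so the retention allowance is not visible in them.

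**Step 2: correct the count, with everyone sampled.** Each aim uses one stratum: 16 × 4 = 64 per arm and 32 × 4 = 128 per factorial side.

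- Factorial, n = 128: 0.40 to 0.44 SD (normal) or 0.41 to 0.45 SD (t, df 62) for ICC 0.1 to 0.2. Power at 0.283 SD, ICC 0.1, is about 50%.
- Arm versus control, n = 64: 0.69, 0.72 and 0.76 SD (t, df 30).

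**Step 3: apply the 25% saliva sample.** 0.25 × 512 = 128 donors, and 128 / 64 = 2 per building. Assuming one smoker and one non-smoker per building, m = 1 for each aim, DE = 1, and the ICC drops out. That leaves 32 per factorial side and 16 per arm.

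| Contrast | Stated | Everyone sampled, correct count (ICC 0.1) | Saliva sample | Saliva sample, 80% retention |
|---|---|---|---|---|
| Factorial, alpha 0.05 | 0.283 SD | 0.41 SD | 0.71 SD (n = 32) | 0.80 SD (n = 25.6) |
| Arm vs control, alpha 0.0167 | 0.472 SD | 0.69 SD | 1.20 SD (n = 16) | 1.36 SD (n = 12.8) |

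(t version throughout.) Before dropout, power is 20% at the stated 0.283 SD and 13% at the stated 0.472 SD. With 80% retention it is 17% and 10%.

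**Step 4: the protocol's own benchmarks, factorial contrast, 32 per side, before dropout.**

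- Smokers: 59.6 / 195.4 = 0.305 SD, power 22%.
- Non-smokers: 0.29 / 0.672 = 0.432 SD, power 40%.

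The detectable 0.711 SD corresponds to 0.711 × 195.4 = 139 ng/mL and 0.711 × 0.672 = 0.48 ng/mL.

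**Sensitivity to the split.** Giving both donors in every building to one aim (64 per factorial side, m = 2) yields 0.53 to 0.55 SD for that aim and leaves the other with no samples. Pooling the strata has the same arithmetic, but with SDs of 195.4 and 0.672 ng/mL it is not a plausible analysis.

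**The case against.** Five points can be made for the plan, or against stronger readings of it.

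1. A reader might infer that the trial was powered as if everyone gave saliva, so that subsampling explains the whole gap. It does not. At ICC 0.1 the factorial figure moves from 0.283 to about 0.41 SD through the doubled count alone, and from there to 0.71 SD through the 25% sampling. The two errors need separate corrections.

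2. A reader might infer that cotinine has no analysis model. The section headed Aim Specific applies repeated-measures generalized linear models to continuous outcomes in general, and the Primary outcome section defines its outcome variable broadly enough to include cotinine. A fuller specification could sit in a document not shown. What stands is narrower: the stated purpose of cotinine there is to check self-report.

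3. Effects in SD units could be carried over to cigarettes per day, which is measured in all smokers and analysed with an identity link. That is fair, but only with 64 per arm and 128 per factorial side. The transfer is weaker for secondhand-smoke hours, which use a log link.

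4. The one-plus-one donor split is an assumption; the documents give only 25% per building and both strata. The ng/mL figures and benchmark powers treat the quoted SDs as those of the analysed outcome, although that outcome is a change and may be transformed. The detectable effects in SD units do not depend on this.

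5. A reader might expect a null cotinine result to be reported as a failed primary outcome. The documents do not say so, and cotinine is one of three listed primaries.

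**Conclusion.** The power statement is wrong as written. The stated effects reproduce only with twice the subjects per aim that the design provides, and the outcome they are stated for is collected in a quarter of participants. For cotinine the detectable effect is about 0.71 SD (factorial) and 1.20 SD (arm versus control), or 0.80 and 1.36 SD at 80% retention, against 0.283 and 0.472 SD stated. These figures rest on an even donor split; the most favourable alternative for one aim's factorial contrast still needs 0.53 SD or more. The claim of sufficient power does not hold for cotinine.

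It would go too far to conclude that the whole trial cannot answer its questions. The self-reported outcomes are planned for everyone in the relevant stratum, where about 0.40 to 0.45 SD (factorial) and 0.69 to 0.76 SD (arm versus control) are detectable before dropout for ICC 0.1 to 0.2. The protocol gives no benchmark on those scales against which to judge these figures.

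**What to change.** - In Sample Size {14}, state the cotinine detectable effects for the actual saliva sample, with the donor split per building and the retention assumption, and remove the claim of sufficient power for cotinine.
- Recompute the section with 64 per arm and 128 per factorial side in each stratum for the self-reported outcomes modelled under Primary outcome, and show the 80% retention allowance explicitly.
- Give cotinine one role across Outcomes {12}, Sample Size {14} and Primary outcome. The validation or secondary role already described in the analysis section is the simplest, since it needs no further assays. Collecting saliva from everyone is an alternative, at assay cost, and would still require the corrected counts.
- Reconcile the status of 7-day secondhand-smoke hours. They are primary under Primary outcome in the statistical methods, but secondary under Secondary outcome and Sensitivity analyses; the secondary list in Outcomes {12} also includes hours of exposure.

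The cost of the wording route is text, with no added participants or assays. The stated power becomes less favourable, and the biomarker may lose primary status. Because recruitment is under way (Implementation {16c}), any change of outcome status is a mid-trial modification that must be reported to the IRB and registry under the amendments section {25}.

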### Trial design {8}

The trial design is a borough-stratified, four-arm, factorial-design, cluster RCT that targets 64 randomly selected buildings (16 buildings per arm) in separate NYCHA developments. We are recruiting and following 8 randomly selected residents stratified by smoking status − 4 smokers and 4 non-smokers - per building (n = 512) into four arms: (1) reduction/cessation, (2) resident endorsement, (3) reduction/cessation plus resident endorsement and (4) the standard approach (128 participants per arm) as shown in Fig. 1. A partnering community-based organization, Health People, Inc., specializing in peer-to-peer health education will train and supervise peer educators (PEs) who will then deliver the designated interventions. Quantitative assessments via survey questionnaire, salivary cotinine measurements, as well as sensory building observations will be used to measure outcomes. We will be evaluating the efficacy of compliance support interventions in reducing personal smoking and exposure to second-hand smoke in public housing. In addition, we will also determine if the tobacco retail environment surrounding a given public housing building moderates the relationship between compliance support interventions and smoking-related outcomes.

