The second stage of enrollment is at the resident level. Participants must be (1) able and willing to provide verbal informed consent, (2) at least 18 years old, (3) able to communicate in English or Spanish, (4) living in the building at least 5 days/week and 9 months/year, and (5) not planning to move in the next 2 years. Participants who (1) have severe physical or mental medical conditions (e.g., cognitive disability) or other factors that could limit participation or ability to give informed consent in the study at baseline or during follow-up visits, (2) participate in focus groups conducted pre or concurrently as RCT that are geared towards understanding how to improve intervention arms for greater impact (buildings identified for focus groups are buildings that will not be assigned an intervention or have recruitment conducted for the main study), or (3) only smoke non-tobacco products (e.g., marijuana) are excluded from participating in the study due to the focus of the study on tobacco products. It should be noted that during the period of recruitment, the smoke-free policy in NYCHA was modified to also include marijuana use. In anticipation of this modification to the smoke-free policy, we are collecting preliminary information regarding marijuana use.

Recruitment of NYCHA residents will be conducted via door knocking and lobby intercepts until the targeted number per group is reached (4 smokers, 4 non-smokers in each building). Smoker status is defined as smoking a tobacco product including e-cigarettes at least 5x/month, and nonsmoker status is defined as never having smoked any product or quit smoking at least 12 months prior to recruitment.

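### The power calculation credits each aim with 128 subjects per arm when 16 buildings of 4 give 64, so power at the stated detectable effects is about 44 to 51%, not 80%

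*Protocol article*

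**What the plan says.** The Trial design section "targets 64 randomly selected buildings (16 buildings per arm) in separate NYCHA developments", recruits "4 smokers and 4 non-smokers - per building (n = 512) into four arms", and arrives at "the standard approach (128 participants per arm"). That 128 is smokers and non-smokers together: 16 × 8. Eligibility Criteria confirms the split: "4 smokers, 4 non-smokers in each building".

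The Sample Size section takes change in salivary cotinine as the powered outcome for Aims 1 and 2. Its starting point is 16 buildings, "with 4 subjects per cluster (smokers for Aim 1, non-smokers for Aim 2) in each arm, we have 128 subjects per group", and it doubles that count to 256 for groups pooled by treatment type. From these counts, for a two-sided test with 80% power, it states detectable effects at ICC 0.1, 0.15 and 0.2 of:

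- 0.283, 0.299 and 0.312 SD with 256 per group at alpha 0.05 (with versus without a treatment type);
- 0.472, 0.499 and 0.524 SD with 128 per arm at alpha 0.0167 (each intervention arm versus control).

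It translates 0.283 SD into 55.3 ng/mL of cotinine for smokers and 0.19 ng/mL for non-smokers. It compares these with outside benchmarks of 59.6 and 0.29 ng/mL and concludes that power is adequate. It adds: "The study is powered on an 80% retention rate, which we have achieved in other studies".

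**The concern.** The sentence contradicts itself. Sixteen buildings with four subjects of one stratum give 64 per arm, not 128, and 128 per factorial side, not 256. The figure of 128 per arm is right only for both strata together, while the sentence assigns smokers to Aim 1 and non-smokers to Aim 2.

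If this were only a slip of wording, the detectable effects could still be right. If the doubled count went into the calculation, every stated effect is too small and the conclusion about power rests on buildings that the trial does not have.

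**Working it through.** **Inputs.** Buildings per arm (16), subjects per building and stratum (4), two-sided test, 80% power, alpha 0.05 or 0.0167, ICC r = 0.1, 0.15, 0.2, and cotinine SDs of 195.4 ng/mL (smokers) and 0.672 ng/mL (non-smokers). All are from Sample Size and Trial design.

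**Formula.** With K buildings per group and m subjects per building,

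SE = √(2[1 + (m − 1)r] / (K m)), in SD units,

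and the detectable effect is (z for alpha/2 + z for power) × SE. The t version replaces the normal with a non-central t, on either cluster df (2K − 2) or subject df (2Km − 2).

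**Step 1: reproduce the stated figures.**

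| Comparison | Clusters × subjects per group | Method | r = 0.1 / 0.15 / 0.2 | Stated |
|---|---|---|---|---|
| Arm | 32 × 4 | t, cluster df | 0.472 / 0.499 / 0.524 | 0.472 / 0.499 / 0.524 |
| Factorial | 64 × 4 | t, subject df | 0.283 / 0.299 / 0.314 | 0.283 / 0.299 / 0.312 |
| Factorial | 64 × 4 | normal | 0.282 / 0.298 / 0.313 | same |
| Factorial | 64 × 4 | t, cluster df | 0.285 / 0.301 / 0.316 | same |

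The arm figures match to three decimals. The factorial figures match approximately, and no single method matches all three. Both need twice the real number of buildings (16 per arm, 32 per side).

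**Step 2: try the alternative.** Pooling strata (8 per building, 16 buildings per arm) gives arm effects of 0.527 / 0.579 / 0.627 (normal) or 0.554 / 0.608 / 0.658 (t, cluster df), and factorial effects of 0.323 / 0.355 / 0.384 (normal). None matches.

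**Step 3: use the actual buildings, one stratum, full enrolment.** At r = 0.1 by the normal method:

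- Factorial: SE = √(2 × 1.3 / 128) = 0.1425; (1.960 + 0.842) × 0.1425 = 0.399.
- Arm: SE = √(2 × 1.3 / 64) = 0.2016; (2.394 + 0.842) × 0.2016 = 0.652.

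| Comparison | Clusters × subjects | Normal | t, cluster df | Power at stated effects |
|---|---|---|---|---|
| Factorial | 32 × 4 | 0.399 / 0.422 / 0.443 | 0.406 / 0.428 / 0.450 | 49–51% |
| Arm | 16 × 4 | 0.652 / 0.689 / 0.724 | 0.685 / 0.724 / 0.760 | 44–48% |

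Stated divided by corrected effect is 0.69 to 0.72, so the stated values are 28 to 31% too small.

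**Step 4: retention.** The stated effects reproduce with 4 per building, the enrolment target. If 20% loss is spread evenly (m = 3.2, an assumption), power at the stated effects on the actual buildings is about 44–46% (factorial) and 37–43% (arm).

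**Step 5: the protocol's benchmarks.** These supposedly have saliva from everyone at full enrolment; t with cluster df, ranges over r = 0.1 to 0.2.

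| Benchmark | In SD | Factorial power | Arm power |
|---|---|---|---|
| Smokers, 59.6 ng/mL | 59.6 / 195.4 = 0.305 | 48–56% | 14–17% |
| Non-smokers, 0.29 ng/mL | 0.29 / 0.672 = 0.432 | 77–85% | 29–36% |

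**The case against.** The core cannot be argued away, but several stronger readings that a reader might infer are not supported.

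- **That the right cotinine figure is now 79 ng/mL for smokers (0.406 × 195.4) or 0.27 for non-smokers (0.406 × 0.672).** These would need saliva from every participant. The Outcomes section and the Plans for assessment section collect it from 25% (n = 128 in the whole trial). The corrected counts fit the self-reported outcomes. For cotinine the position is worse: with one sample per stratum per building (an assumption), the normal method gives about 0.70 SD (factorial) and 1.14 SD (arm).
- **That the retention statement is false.** The software inputs are not shown. What can be said is that the counts equal the enrolment targets and no allowance is visible.
- **That the adequacy claim fails everywhere.** For the non-smoker benchmark the factorial comparison keeps roughly 77–85% power before attrition on the full stratum, so the double count alone does not overturn it there.
- **That the planned analysis has 44–51% power.** That is the power of the simple two-mean comparison the protocol itself used. The planned model is a repeated-measures GEE, and the inputs needed for its power are not given.
- **That a null result will be over-read.** The protocol sets no rule for reading a null result, so this would be speculation.

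The choice of test also moves the figures a little, which is why ranges are given. No variant tried brings the actual design near 80%.

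**Conclusion.** The stated sample counts are wrong for both aims, and the error entered the computed effects. On the actual 16 buildings per arm, the detectable effects are about 0.40–0.45 SD (factorial, alpha 0.05) and 0.65–0.76 SD (arm versus control, alpha 0.0167). The stated effects therefore have about half the chance of detection, or a little less, rather than 80%. This rests on the protocol's own ICC range, full enrolment, equal building sizes and a simple comparison of two means; the ranges span the normal and cluster-df t methods. Attrition would lower the power further.

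The statement of adequate power does not hold for the smoker benchmark in either comparison, nor for either benchmark in arm-versus-control comparisons. It remains broadly tenable only for the non-smoker benchmark in the factorial comparison, and then only if the outcome were measured in everyone.

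**What to change.** In Sample Size:

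1. Replace 128 and 256 with 64 and 128 per smoking stratum. After 20% loss these are about 51 and 102 (0.8 × 64 = 51.2; 0.8 × 128 = 102.4).
2. Restate the detectable effects in SD units from the actual clusters, for outcomes measured in everyone: self-reported cigarettes per day (Aim 1) and self-reported secondhand smoke exposure (Aim 2). Name the method and df.
3. Either name one of those as the powered outcome, or keep cotinine and recompute its effects and ng/mL translations for the 25% saliva subsample. Do not present 79 or 0.27 ng/mL as the trial's detectable cotinine difference.
4. State the retention allowance actually used, and how loss was assumed to fall across buildings.
5. Qualify the adequacy sentence by aim and by comparison.

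The cost is text and a short recalculation, with no extra enrolment. The downside is less favourable stated figures.
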